### Interventions

The heart of our interventional setup is a non-invasive electroencephalography (EEG)-based BCI that governs the activation of two actuators: a robotic glove and multi-channel FES.

#### Materials

Brain activity is recorded from a 16-channel electroencephalogram (16 Channel V-amp system, Brain Products GmbH, Gilching, Germany; Ag/AgCl electrodes on ActiCAP 10–20 system) covering the motor cortex of both hemispheres. The signals are sent to an external decoder that classifies if the incoming signal corresponds to a motor intention for the affected limb. When this condition is met, the two actuators (the exoskeleton and the FES) are triggered. The exoskeleton is a Gloreha Sinfonia (Idrogenet, Brescia, Italy) consisting of a cable-driven glove that can be used to flex and extend fingers (36). Thanks to the embedded stretch-sensors, we are able to monitor voluntary activation and perform assisted-as-needed movements. The proximal upper-limb can be activated by supra-motor threshold FES (Rehastim, Hasomed Germany with PALS electrodes, Axelgaard, Denmark) at seven different muscles: rhomboids, deltoid anterior and medialis, biceps brachialis, triceps, brachioradialis and extensor digitorum. Stimulation can be given to each muscle individually or in combination.

During *IP2*, anodal tDCS (DC-stimulator, Neuroconn, Ilmenau, Germany) is focally applied to the motor cortex of the lesioned hemisphere. The stimulation is applied through a 4 × 1 montage (51) where the anode is placed over the C3 (or C4) position according to the 10–20 EEG-system. The 4 cathodes are equally distanced around it and placed at the positions of CP5, CP1, FC1, FC5 (or CP6, CP2, FC2, and FC6). EEG electrodes and tDCS electrodes will be exchanged during therapy and custom-made hybrid holders have been created. The exact position of the electrodes is based on simulation results using SimNIBS 3.0 (52). In these simulations, we aimed at optimizing electrodes' location in terms of highest current density peak and broad and strong activation of primary motor and somatosensory cortices, while considering physical constraints for placing electrodes without creating bridges. The Ag/Ag-Cl electrodes (12 mm diameter) are placed, with electrolytic gel, in the EEG cap used for brain activity recording. More details on the functioning and setup of these different technologies are reported in the Supplementary Material.

#### Interventional Session

One interventional session lasts approximately 2.5 h and includes setup, calibration, therapy, and assessment of the sFM-UE, if required. The full session is performed by a trained study therapist and run from a graphical user interface (see Supplementary Material).

#### Set-Up

The patient sits in a comfortable chair in front of a screen. The impaired arm is placed on an antigravity support (Armon arm, integrated with Gloreha Sinfonia system) with the elbow flexed at around 90°. Electrodes for FES are placed over the bellies of the muscles of interest and the impaired hand is inside the glove exoskeleton in anatomical rest position (Figure 2).

**Figure 2 F2:**
[figure not shown]
Interventional setup. The patient is sitting on a comfortable chair with the arm resting on an anti-gravity support; multiple FES electrodes are placed over the upper-limb; and the hand is placed in the robotic glove, which the therapist is adjusting. The subject is wearing an EEG cap for the BCI. On the computer screen the in-house application through which the therapy session can be run is visible.

#### Calibration Procedure

At each new session, both the BCI and the actuators need to be calibrated. For the former, we seek a high accuracy (i.e., at least 70% offline) in classifying motor intention of the affected upper-limb. For the latter, given the synergistic work of the exoskeleton and the FES, we aim at combining them to artificially generate smooth movements that strongly resemble natural ones. This requires a fine-tuning of the actuators in terms of activation time and intensity. See Supplementary Material for further details.

#### tDCS

If in I*P2*, anodal tDCS is given at 2 mA (with 8 seconds ramp-up and ramp-down at the beginning and end respectively) for 20 min when the patient is at rest before the BCI-based rehabilitation.

#### Therapy

For each session, the study therapist chooses the exercises from a broad range of possibilities including simple movements (e.g., hand opening and closing) and functional exercises (e.g., reach and grasp a cup); the full list is available in the Supplementary Material. The patient then receives instructions on a video screen indicating the exercises that he/she has to follow. For each repetition of each exercise, as soon as the BCI decoder classifies a movement intention the actuators are initiated.

### Assessments

Longitudinal multimodal data is gathered during the different visits. The full procedure and tests can be seen in Figure 1. Baseline characteristics describing patients' demographics are performed right after the inclusion. Clinical assessments are performed at the observation visits, the full evaluation visits as well as at follow-up (i.e., 3 months after end of treatment). Neural correlates of motor impairments are performed at the full evaluation visits in T0, T1, and T2 (see Figure 1 for full procedure).

#### Observational Period

Given the absence of a control group, 10 randomized patients will also do, in addition to the standard protocol, a 3-month observational period prior to the intervention to further validate that the targeted population is in the plateau phase of recovery with a stable level of motor impairment, as suggested in the literature.

Upon recruitment, patients are randomized with a one-to-two distribution into the waiting or the starting group. The waiting group (*n* = 10) corresponds to the patients doing first the observational period and then starting the treatment phase; the starting group (*n* = 20) will directly begin with the treatment phase. The waiting group undergoes an observational period of 3 months prior to beginning the treatment, whereas the starting group begins the treatment immediately. Once the intervention starts, both groups continue the procedure in the same way and receive the same treatment described in the previous paragraphs.

The assignment of patients (waiting or starting group) is performed per center and takes age group (before 50, between 50 and 65, and over 65) and side of impairment into account (53).

#### Blinding Procedures

Complete blinding cannot be achieved in this study design (i.e., patients know in which group they have been placed – waiting vs. starting group, though the treatment phase is identical for both groups). The therapist performing the interventions is blinded to the scores given at the evaluation visits by the assessor. Within the protocol, there is at least one trained therapist per study site. The therapist assigned to one study site performs the intervention and assesses the sFM-UE for all patients belonging to the same site. An assessor, not involved in any way in the treatment (i.e., blinded to therapies' outcomes and sFM-UE) conducts the assessments at the full evaluation visits (T0, T1, and T2). The therapist of one site takes the assessor role for the other site for the clinical measures.

#### Baseline Characteristics

At baseline, descriptive information such as: age, time since stroke, affected side, medication use, and comorbidities are acquired. Furthermore, the MoCa (54), a full neurological exam, the NIHSS (41), the Cumulative Illness Rating scale (42), the Bells cancellation test (37), apraxia screening of TULIA (38), language screening test for aphasia (39), and the motricity index (40), are conducted.

#### Clinical Assessments

An assessment battery covering motor impairment at the functional, activity and participation level and several relevant other domains is conducted at each time point. The battery consists of: FM-UE (35), Action Research Arm Test (44), modified Ashworth scale (MAS) (43), Medical Research Council scale (MRC), subsections of phasic alertness and divided attention of the test of attentional performance (46), Stroke Impact Scale 3.0 (47), Beck Depression Inventory scale (48), Rivermead Assessment of Somatosensory Performance (45), and Multidimensional Fatigue Inventory (49). During the full evaluation visits (T0, T1, T2), sleep is monitored with an ActiGraph device (wGT3X-BT, Florida, USA) combined with the Pittsburgh sleep quality index (50) and a sleep diary. The FM-UE is instrumented with wearable 3D motion capture sensors (Xsens MVN, Enschede, Netherlands) and electromyography (EMG) sensors (Noraxon, Arizona, USA), and videotaped. The instrumented FM-UE can provide kinematic data and thus further evaluation of motor improvement on the same movements of the primary outcome scale; for example, information regarding smoothness and speed of movement (55, 56) will be retrieved and analyzed. Having recordings of the FM-UE will give the possibility (if necessary) to have an additional assessor evaluating the scale used for the primary outcome. For more information on the instrumented FM-UE, see the related paragraph in the Supplementary Material. Finally, an in-house self-questionnaire is used to evaluate how patients felt about the therapy and their expectancies.

#### Neural Correlates of Motor Improvement

In addition to the clinical scales, we will use multi-modal neuroimaging and electrophysiological techniques to study the underlying mechanisms of rehabilitation. We perform structural and functional (resting-state and task-related) magnetic resonance imagining (MRI). Electrophysiological parameters will be measured with EEG, transcranial magnetic stimulation (TMS), TMS-EEG and EMG. See Supplementary Material for details of the MRI-based neuroimaging and the electrophysiological protocols. Analyses of TMS/TMS-EEG evoked potential features, such as motor evoked potentials (MEPs) global and local mean field power will be determined. Regarding the neuroimaging data, factors such as the corticospinal integrity, whole brain connectivity and disconnectivity will be investigated with structural MRI; resting state fMRI allows to determine changes in resting state connectivity and with task-based fMRI, functional connectivity analyses will be performed. Electrophysiological and neuroimaging exams are performed by trained scientists and study therapists.

### Population Size

The study aims to recruit 40 patients, which by taking into account an estimated 20% dropout, leads to 30 patients completing the study with 10 starting in the waiting group (2:1 design). This number was obtained through an a-priori power analysis for sample size in G-Power (57) for a paired Wilcoxon Signed Rank test considering an alpha and beta of 0.05 and expecting an effect size of 0.64 (i.e., considering a mean FM-UE of 15, standard deviation of 4.7 (58) and expected improvement of 4 points). The sample size is also in agreement with previous neurotechnology-related studies and considering that the study is a proof of concept.

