## Abstract

Effective, patient-tailored rehabilitation to restore upper-limb motor function in severely impaired stroke patients is still missing. If suitably combined and administered in a personalized fashion, neurotechnologies offer a large potential to assist rehabilitative therapies to enhance individual treatment effects. AVANCER (clinicaltrials.gov NCT04448483) is a two-center proof-of-concept trial with an individual based cumulative longitudinal intervention design aiming at reducing upper-limb motor impairment in severely affected stroke patients with the help of multiple neurotechnologies. AVANCER will determine feasibility, safety, and effectivity of this innovative intervention. Thirty chronic stroke patients with a Fugl-Meyer assessment of the upper limb (FM-UE) <20 will be recruited at two centers. All patients will undergo the cumulative personalized intervention within two phases: the first uses an EEG-based brain-computer interface to trigger a variety of patient-tailored movements supported by multi-channel functional electrical stimulation in combination with a hand exoskeleton. This phase will be continued until patients do not improve anymore according to a quantitative threshold based on the FM-UE. The second interventional phase will add non-invasive brain stimulation by means of anodal transcranial direct current stimulation to the motor cortex to the initial approach. Each phase will last for a minimum of 11 sessions. Clinical and multimodal assessments are longitudinally acquired, before the first interventional phase, at the switch to the second interventional phase and at the end of the second interventional phase. The primary outcome measure is the 66-point FM-UE, a significant improvement of at least four points is hypothesized and considered clinically relevant. Several clinical and system neuroscience secondary outcome measures are additionally evaluated. AVANCER aims to provide evidence for a safe, effective, personalized, adjuvant treatment for patients with severe upper-extremity impairment for whom to date there is no efficient treatment available.

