### Study Procedure

All thirty planned patients will receive a cumulative neurotechnologies-based intervention: (1) Interventional phase 1 (IP1) uses a BCI to control supra-motor threshold FES for the upper-limb and a hand exoskeleton for flexion and extension of the fingers with arm support; (2) Interventional phase 2 (IP2) adds tDCS to IP1.

The duration of both interventions is tailored for each patient and is determined according to improvement monitored through a short version of the FM-UE (sFM-UE) (35), consisting of 54 points excluding reflexes and coordination items. This short FM-UE is assessed every second session of intervention. The patient is considered to have no further prospect of recovery when no improvement in terms of sFM-UE is seen in the current session (Si), defined by:

(1)
$$\begin{array}{r} {\text{sFMUE}}_{\text{Si}}\;\leq \text{ median}\left({\text{sFMUE}}_{\text{Si}-2},\;{\text{sFMUE}}_{\text{Si}-4},\;{\text{sFMUE}}_{\text{Si}-6}\right) \end{array}$$

When this condition is met, the intervention changes to a second stage and the same procedures take place to determine the end of *IP2*. A minimum of 11 sessions per intervention is provided and equation (1) is thus applied from the eleventh session of both phases. The session counting of *IP1* begins when the patient can govern the BCI (i.e., reaching 70% of accuracy in offline model validation); this choice is made to have a similar amount of *valid* therapy sessions in the two interventional phases. In addition to the therapies, every subject participates in three multimodal assessment visits: before *IP1* (T0), at the change to the second interventional phase (T1), and at the end of *IP2* (T2). A follow-up visit is scheduled 3 months after the end of *IP2*. The full procedure can be seen in Figure 1. Visits and interventions are conducted at the centers, in our laboratory spaces. Only screening and observation visits may be done at the patient's place of residence.

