### Statistics

To evaluate if significant motor improvement of the upper-limb is achieved, the FM-UE scores of all the 30 patients will be compared between the final (T2) and the initial (T0) evaluation visits: we will use a two-tail paired Wilcoxon Signed Rank test, with the probability value set at 0.05. The null hypothesis is H0 = “FM-UE scores at T2 and FM-UE scores at T0 follow the same distribution”, H1 = “FM-UE scores at T2 do not follow the same distributions of scores at T0; the distributions are significantly different”. H0 will be rejected if a *p-*value < 0.05 is obtained. This evaluation will be considered together with the expected four-point improvement on average.

To assess if the observed changes in the FM-UE are long-lasting, we will compare with the same test (Wilcoxon Signed Rank, alpha = 0.05) the FM-UE scores at T2 with those acquired at the follow-up (3 months after T2). Another related secondary outcome regards the validation of motor function stability of chronic stroke patients (i.e., no FM-UE improvement during the observation period). We will use a Kruskal-Wallis test with alpha at 0.05 to investigate differences in the FM-UE scores at the three time points of the observation period. We do not expect to reject the null hypothesis for which the three groups are said to come from the same distribution.

Among the most important secondary outcomes is safety and feasibility; for these, descriptive statistics will be provided. One major safety outcome is incidence of epileptic seizures during the intervention period with tDCS, as well as other SAEs. Furthermore, feasibility will be determined by the drop-out rate, usually in clinical trials set to up to 20%.

Important exploratory analyses will focus on the difference between the two interventional phases; such investigation might give an insight on the role of tDCS in the rehabilitation. To test the effect of dose and intervention type on the FM-UE we will use a mixed effects linear model with random effect of subject and fixed effects of session, intervention type and the interaction of the two. If significant results will be observed, we can then build on this initial model by adding more independent variables such as lesion location and time post-stroke. Other analyses will correlate the multimodal data acquired during the three full evaluations (T0, T1, T2), such as corticospinal tract integrity and the TMS evoked potential, with the clinical scales.

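### The recruited and randomised sample size is inconsistent: Population Size recruits 40 for 30 completers, while the Abstract, Study Procedure and Observational Period use 30

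*Protocol article*

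**What the plan says.** All places are in the protocol article.

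- **Population Size** is the only section that separates recruited from completing patients: "The study aims to recruit 40 patients, which by taking into account an estimated 20% dropout, leads to 30 patients completing the study". Ten of these completers are counted to the waiting group.
- **Abstract:** "Thirty chronic stroke patients with a Fugl-Meyer assessment of the upper limb (FM-UE) <20 will be recruited at two centers".
- **Study Procedure:** "All thirty planned patients will receive a cumulative neurotechnologies-based intervention". The opening of Methods and Analysis adds that everyone recruited receives the intervention.
- **Observational Period:** "Upon recruitment, patients are randomized with a one-to-two distribution into the waiting or the starting group". The group sizes given there are 10 waiting and 20 starting.
- **Statistics:** the primary test compares T2 with T0 in 30 patients. The closing paragraph limits the main analyses to patients who finished the protocol. On feasibility: "feasibility will be determined by the drop-out rate, usually in clinical trials set to up to 20" percent.

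**The concern.** Two recruitment totals are in print, 40 and 30. The figure 30 is attached in turn to patients recruited (Abstract), planned for treatment (Study Procedure), randomised at recruitment (Observational Period), completing (Population Size) and analysed (Statistics). These can all be the same number only if nobody drops out, and the plan assumes that one in five will.

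The total matters because the analysis uses completers only, so each dropout reduces the primary analysis set. A site that followed the Abstract would stop recruiting at 30 and would probably fall short of the 30 completers that the power calculation needs. The waiting group would shrink as well, and it is the trial's only source of data on the natural course. The drop-out rate, which is the stated measure of feasibility, would also have two possible denominators.

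**Working it through.** **Inputs.** Recruitment 40, dropout 20%, completers 30, effect size 0.64, alpha 0.05 and beta 0.05 (Population Size); recruitment 30 (Abstract); 1:2 randomisation with group sizes 10 and 20 (Observational Period); two-tailed Wilcoxon signed-rank test (Statistics).

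**1. The plan's own step from 30 to 40.**
- Recruits needed for 30 completers: 30 / (1 − 0.20) = 37.5, so 38. The plan says 40.
- Completers expected from 40: 40 × 0.80 = 32. The plan says 30.
- Dropout implied by exactly 30 of 40: 1 − 30/40 = 25%.

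The stated pair differs from the exact result by two patients, on the safe side. It is reproduced to within rounding.

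**2. The total across sections.**
- Observational Period: 10 + 20 = 30 randomised at recruitment.
- Population Size: 40 recruited.
- Difference: 10 patients, which rounding does not explain.
- 40 randomised 1:2: 40/3 = 13.3 waiting and 26.7 starting, so about 13 and 27.
- After 20% dropout: 13 × 0.8 = 10.4 and 27 × 0.8 = 21.6. The printed 10 and 20 therefore fit completers of a 40-patient trial, but not patients randomised in one.

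**3. If the Abstract's 30 were followed.**
- Completers: 30 × 0.80 = 24.
- Waiting-group completers: 10 × 0.80 = 8.

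**4. Power.** The signed-rank test is approximated by a paired t-test with effective size m = n × 3/π (its relative efficiency under normality, 0.955), noncentrality 0.64 × √m, m − 1 degrees of freedom and alpha 0.05.

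| Completers n | m | Noncentrality | Two-sided power | One-sided power |
|---|---|---|---|---|
| 24 | 22.9 | 3.06 | 83% | 91% |
| 30 | 28.6 | 3.43 | 91% | 95.5% |
| 32 | 30.6 | 3.54 | 93% | 96.5% |

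With other efficiency assumptions (0.864 up to 1), two-sided power runs from 79% to 85% at 24 completers and from 88% to 92% at 30.

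The planned 95% is reached at 30 completers only with a one-sided test; the two-sided test needs 36. That is a separate matter. The loss that belongs to this point is the step from 30 to 24 completers: about 91% to 83% two-sided, or 95.5% to 91% one-sided.

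**The case against.** **The documents partly reconcile themselves.** Population Size ties both the 30 and the 10 in the waiting group to patients who complete, and Statistics analyses finishers. On that reading 40 is the recruitment target and 30 the completer target, and the other sections use the completer figure loosely. This is probably what was meant, and it shows which number to keep. It does not remove the conflict: the Abstract attaches thirty to recruitment, and Observational Period sets the group sizes at randomisation, before dropout can occur. Nor does condensation into an article explain it, because the conflicting figures are printed rather than left out.

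**Two stronger readings are tempting and not supported.**

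- A reader might infer that the dropout allowance is wrong, because 40 less 20% is 32. The subtraction is right, but the difference is two patients in the conservative direction, and 30 reads naturally as the number required. The wording is loose, but nothing in the design is harmed, and there is no reason to lower the target of 40.
- A reader might infer that the plan fails its own feasibility limit, because 30 of 40 is 25% dropout. The plan nowhere assumes 25%. Statistics gives 20% as what is customary in trials, for an outcome to be reported descriptively, and not as a pass/fail rule for this one. The article could also leave the denominator of that rate to the full protocol. It is worth stating here only because two totals are in print.

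**Conclusion.** The point holds as an inconsistency in the recruited and randomised sample size: 40 in one section and 30 in three others, a gap of ten patients. It does not show that the trial is underpowered as intended. With 40 recruited and 20% dropout, 32 complete, more than the 30 required.

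The harm arises if the 30 is taken as the recruitment target. About 24 patients, 8 of them waiting, would then enter the completers-only analysis, with about 83% two-sided power against a planned 95% (about 91% with 30 completers). These figures assume exactly 20% dropout, equal in both groups, the stated effect size of 0.64, and near-normal differences for the efficiency of the signed-rank test. The correction should be made, and it is simple.

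**What to change.** - **One total.** State in the Abstract, Study Procedure, Observational Period and Population Size that 40 patients are recruited and randomised 1:2, about 13 waiting and 27 starting.
- **One completer target.** State that at least 30 completers are required and that 32 are expected at 20% dropout. Note that 30 of 40 would correspond to 25% dropout.
- **Abstract and Study Procedure.** Change the thirty recruited, and the thirty planned for treatment, to 40, or say expressly that thirty is the number of completers.
- **Observational Period.** Label 10 and 20 as completers, or replace them with the randomised sizes.
- **Statistics.** Say that the 30 analysed are the minimum number of completers, and calculate the feasibility drop-out rate as dropouts divided by all randomised patients.

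The cost is wording only. No patients are needed beyond the 40 already planned, and the primary test and its analysis set do not change.

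### The sample-size statement does not reproduce: the printed inputs do not give an effect size of 0.64, and 30 patients give 95% power for a one-tailed test (normal parent), not for the planned two-tailed test

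*Protocol article*

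**What the plan says.** Population Size says the number of patients came from an a priori G-Power calculation for a paired signed-rank test, "considering an alpha and beta of 0.05 and expecting an effect size of 0.64". It explains that effect size in a bracket: "considering a mean FM-UE of 15", "standard deviation of 4.7 (58) and expected improvement of 4 points". The result is 30 completers. The section does not say whether alpha is one- or two-tailed. It gives no T0–T2 correlation or SD of the change, and no parent distribution for the signed-rank calculation.

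The Statistics section defines the primary analysis on the 30 patients, T2 against T0: "we will use a two-tail paired Wilcoxon Signed Rank test, with the probability value set at 0.05".

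**The concern.** A paired test is powered on the mean change divided by the SD of the change. The article gives a mean change (4 points) and an SD that reads as the SD of the FM-UE score, because it stands next to a mean score of 15. Neither that SD used directly nor the same SD with uncorrelated visits returns 0.64. The reader therefore cannot tell what variability of change was assumed, and that assumption drives the sample size.

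Separately, 30 looks like a one-tailed result, while the primary test is two-tailed. If so, the claimed 95% power belongs to a test that will not be run. This is the only formal power claim for the primary endpoint.

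**Working it through.** **Inputs.** From Population Size: alpha 0.05, beta 0.05 (power 0.95), effect size 0.64, SD 4.7, expected improvement 4 points, 30 completers. From Statistics: two-tailed signed-rank test at 0.05. The mean of 15 does not enter a paired effect size.

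**1. Effect size**

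- Taking 4.7 as the SD of the change: 4 / 4.7 = 0.851.
- Taking 4.7 as the SD of the score at both visits, with correlation r: SD of change = 4.7 × √(2(1 − r)).
  - r = 0: SD of change 6.647, effect size 4 / 6.647 = 0.602.
  - r = 0.5: SD of change 4.7, effect size 0.851.
- Working back from 0.64: SD of change = 4 / 0.64 = 6.25, so r = 1 − (6.25 / 4.7)² / 2 = 0.116.

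So 0.64 requires a quantity that is not printed. On the equal-SD reading, that quantity is a T0–T2 correlation of about 0.12. This is low for patients whom the article describes as being on a stable plateau, although varied response to treatment would also lower it.

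**2. Reproducing the 30**

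Method: signed-rank power by asymptotic relative efficiency (ARE). The effective n is N × ARE, and power comes from the noncentral t distribution with df = N × ARE − 1 and noncentrality d × √(N × ARE). For a normal parent, ARE = 3/π = 0.955.

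At N = 30 and d = 0.64, the effective n is 30 × 0.955 = 28.65 and the noncentrality is 0.64 × √28.65 = 3.43.

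| d = 0.64, alpha 0.05 | N for 95% power | Power at N = 30 |
|---|---|---|
| One-tailed, normal parent | **30** | 95.5% |
| Two-tailed, normal parent | **36** | **91.1%** |
| One-tailed, plain paired t | 28 | 96.2% |
| Two-tailed, plain paired t | 34 | 92.3% |
| One-tailed, minimum ARE (0.864) | 33 | 93.6% |
| Two-tailed, minimum ARE (0.864) | 40 | 87.9% |

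The plan's figure is matched exactly by the one-tailed, normal-parent row. A simulation of the signed-rank test on normal differences (20,000 runs, normal approximation for the p-value) gave 95.6% one-tailed and 91.2% two-tailed at N = 30. Two-tailed power in the simulation reached 95% at 35 to 36 patients.

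**3. Two-tailed results under the other readings of 4.7 (normal parent)**

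| Assumption | Effect size | N for 95% power | Power at N = 30 |
|---|---|---|---|
| 4.7 is the SD of change | 0.851 | 21 | 99.3% |
| SD of change 6.25 (implied by 0.64) | 0.64 | 36 | 91.1% |
| 4.7 is the score SD, r = 0 | 0.602 | 40 | 87.4% |

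For 30 completers to give 95% two-tailed power, the effect size would have to be about 0.70.

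**The case against.** Four points can be made for the plan.

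- **The inputs are incomplete rather than wrong.** The article does not literally claim 0.64 = 4/4.7, and with r of about 0.12 the printed figures are compatible with 0.64. A condensed article may leave the correlation to the full protocol. This is fair as far as it goes. But the article chose to print a derivation, with 0.64 presented as following from those inputs, and it does not follow from them.
- **Sidedness is inferred.** Population Size never says one-tailed, and other parent distributions change the result. Two-tailed at 0.64, a logistic parent gives N = 31 (94.5% power at 30) and a Laplace parent gives N = 23 (98.7%). This stands as a qualification: the one-tailed conclusion assumes a normal parent. Neither alternative is mentioned in the article, however, and neither returns 30.
- **The loss is small.** Power of 91% is respectable. If 40 are recruited and the stated 20% drop out, 40 × 0.8 = 32 complete, with two-tailed power of 92.8%. If r is 0.5 or more, power is at least 99%. All true, and it is why no change in sample size is needed. Even with 32 completers, though, the stated 95% is not reached at 0.64.
- **Proof of concept and precedent also support the size.** They may justify 30 patients. They do not make the stated power correct.

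**Conclusion.** The statement is wrong as written, on both counts.

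- The printed inputs give 0.85 if used directly and 0.60 at zero correlation. Reaching 0.64 needs an unstated SD of change of 6.25.
- At 0.64 with a normal parent, 95% power with 30 patients belongs to a one-tailed test. The planned two-tailed test has about 91% power (88% under the minimum-efficiency setting) and needs 36 completers for 95%.

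Depending on which printed figure is trusted, 0.64 or 4/4.7, the two-tailed requirement runs from 36 down to 21 patients.

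This rests on the normal-parent assumption and, for the correlation of 0.12, on equal SDs at T0 and T2. What the cited SD of 4.7 describes cannot be checked from the article. The type I error and the planned analysis are unaffected. The fault lies in the stated power and its basis, and the practical loss is about 4 percentage points at 0.64.

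**What to change.** Rewrite the power paragraph in Population Size so that it agrees with Statistics. State two-tailed alpha 0.05, 30 completers and the parent distribution used. Identify the SD as that of the T0–T2 change, and give the assumed T0–T2 correlation if it is derived from a score SD. Then give the matching power:

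- if 0.64 is kept: SD of change 6.25 (the value implied by 4 points and 0.64) and power about 91%; or
- if the SD of change is believed to be 4.7: effect size 0.85 and power about 99%.

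The sponsor should choose by checking what the original calculation and the cited source actually used. If 95% two-tailed power at 0.64 is wanted instead, the target becomes 36 completers, or 36 / 0.8 = 45 recruited at 20% dropout.

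Restating costs one paragraph, and if 0.64 is kept the stated power becomes slightly less favourable. It requires no change to enrolment, conduct or analysis.
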